### Statistical analysis

All analyses will be performed for each of the completed data sets and the results will be appropriately pooled. For the medical outcomes a conditional linear or Cox regression analysis will be chosen as appropriate for the outcome. For the Cox regression analysis, the proportional hazards assumption will be tested with Schoenfeld residuals. For the psychological outcomes linear mixed-effects models will be used.

For donor subgroup analysis, parametric and non-parametric tests will be chosen as appropriate for descriptive comparisons, Cox regression analysis will be chosen to investigate different outcomes, and mixed models will be chosen for repeated variables, e.g. kidney function and quality of life.

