## Methods

### Participants and procedure - live kidney donors

The Netherlands has the highest number of live kidney donor transplantations in Europe spread over eight kidney transplant centers, with an annual living donation rate of 31.0 per million population in 2013 [30]. Over the years the Erasmus University Medical Center has developed the largest live kidney donation program of its country with approximately 140 procedures per year and is the referral center for other transplant centers in the country. In 2014, a total of 397 live kidney donor transplantations were performed in the Netherlands [31]. Thirty-five percent of these procedures were performed at Erasmus University Medical Center. All donors who donated a kidney from 1981 through 2010 at the department of Surgery of the Erasmus University Medical Center or who had their full medical work-up here prior to donation, but donated in another transplant center because of their participation in the national kidney exchange transplant program will be eligible to be included in this study. All donors were screened preoperatively by a nephrologist, transplant surgeon, anesthesiologist, and social worker and underwent imaging by renal angiography, magnetic resonance imaging or computerized tomography scan. Since 1981, data on pre-donation characteristics such as prior medical history, medication use, BMI, as well as blood and urine analysis regarding kidney function have been collected. Furthermore, consecutive donors included in two randomized controlled trials on surgical techniques between 2001–2004 and 2008–2010 [4, 32, 33] have completed questionnaires on quality of life pre-donation and at set times after the procedure, using the SF-36 questionnaire and EuroQoL questionnaire. Donors are monitored annually on their kidney function by blood- and urine analysis, blood pressure, weight and other current medical issues at the department of Nephrology of the Erasmus University Medical Center or another hospital, or by their general practitioner. Up to 2011, this database comprises 1092 live kidney donors. Approval of the Medical Ethical Committee was obtained (MEC-2012-519). Pre-donation characteristics on kidney function, BMI, pre-existing co-morbidity and medication of all donors will be updated in accordance with the hospital’s electronic patient system. Mortality will be checked in accordance with the Municipal registry. All donors who are alive will be invited by post to visit the outpatient clinic of one of three hospitals in different regions of the Netherlands for an extensive follow-up appointment, supplementary to their yearly check-up. During the study-visit the donor and study investigators will sign the consent form. During their study-visit, blood and urine will be collected for analysis and donors will undergo two interviews regarding quality of life and their psychological well-being. Furthermore, an ultrasound of their remaining kidney will be performed to measure the size. Participating donors will be reimbursed for their travel costs. Unexpected outcomes will be reported to both the donor and the treating nephrologist, who will initiate subsequent examinations and treatment if needed. The general practitioner and any other treating specialist(s) will be notified if needed. Non-responders will be contacted once again and non-participants will be asked to fill out and return a questionnaire on their medical history and quality of life. In addition, non-participants will be asked to give permission to request recent laboratory results on kidney function and new-onset co-morbidities from their medical records, in order to analyze a potential selection bias. To strengthen our results, we aim for a response of 70 percent or higher. All private data are anonymized by allocating a study number. The coordinating investigators and the principal investigator are the only ones who have access to the coding system. All data will be entered into a database, which is managed by the coordinating investigators. At the end of the study all data will be analysed together with the trial statistician (DR).

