
### Participants and procedure - non-donors

Non-donors will be selected from the Study of Health in Pomerania (SHIP) [34, 35] and the Rotterdam Study [36, 37], both population based cohort studies to cover the whole age range of our donors.

SHIP is a population-based cohort study initiated in 1997 among inhabitants of West Pomerania in the north-east of Germany. Two main objectives of this study were first to assess prevalence and incidence of common risk factors, subclinical disorders and clinical diseases, and second to investigate the complex associations among these [34, 35]. Data on kidney function, blood pressure, BMI, medication, incidence of cardiovascular disease and diabetes, psychological well-being and quality of life have prospectively been recorded [34]. SHIP comprises two cohorts aged 20–79 years. In our matched study, the first cohort will be used due to the longer follow-up (*n* = 4308). Multiple follow-up examinations of this first cohort were conducted between 1997 and 2015.

The Rotterdam Study is a prospective cohort study that started in 1990 in Ommoord, a neighborhood in Rotterdam, the Netherlands. The study targets cardiovascular, endocrine, hepatic, neurological, ophthalmic, psychiatric and respiratory diseases [36, 37]. As of 2008, 14,926 subjects aged 45 years or over were included. Data such as hypertension, serum creatinine, serum eGFR, cardiac events, mortality, diabetes, quality of life and psychological well-being have prospectively been recorded [37]. The Rotterdam study comprises three different cohorts. We will use the second and the third cohort to select non-donors (*n* = 6943), since these comprises more study parameters compared to the first cohort. Multiple follow-up examinations of these two cohorts were conducted between 2000 and 2012. Given the size of both studies, sufficient data on all study parameters will be available in our reference group.

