All these variations might explain the contradictory results. As donors are a highly selected healthy population, comparison to the general population might lead to an underestimation of long-term risks [16]. For this reason, a study on long-term outcome, including baseline data and a well-matched non-donor group, is the design of choice. In the design of our study we tried to adhere to suggestions of authors of these previous studies. The current donor-cohort of our study forces us to use two different population-based cohort studies to form our non-donor group, as no single population-based study incorporating representative individuals with a broad enough age range provided the desired set of parameters. Nevertheless, this design will facilitate in a one to four proportion. Previous studies in our center in the same living donor population have always resulted in a high response [5, 6, 27, 47]. Although a selection bias can never be precluded, analysis of the non-responding group should provide us with an indication of whether the sample is representative. Our study population includes elderly donors and donors with minor co-morbidity. As there is currently little research on these sub-groups, this study should clarify the ambiguities concerning the long-term outcomes in these groups.

With this study we will try to overcome the limitations of previous studies. We aim to assess the long-term consequences of live kidney donation after a decade post-donation. This study will compare donors with a matched group of non-donors, regarding kidney function, kidney-related comorbidity, quality of life and psychological outcomes.

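### Follow-up time is not aligned between donors (about 2 to over 30 years) and non-donors (at most 12 or 18 years), and the stated between-group model for kidney function cannot separate attained age, step loss and later decline

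*Protocol article*

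**What the plan says.** The primary outcome is serum creatinine and CKD-EPI eGFR (Protocol article, Outcome measures). No time point is named.

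- **Donors** (Participants and procedure - live kidney donors). Eligible are "All donors who donated a kidney from 1981 through 2010 at the department of Surgery of the Erasmus University Medical Center", plus those worked up there who donated elsewhere through the exchange programme. Living donors are invited "for an extensive follow-up appointment, supplementary to their yearly check-up". The yearly check-ups are described as: "Donors are monitored annually on their kidney function by blood- and urine analysis, blood pressure, weight and other current medical issues". These may take place at Erasmus, at another hospital or with the general practitioner.
- **Non-donors** (Participants and procedure - non-donors). Rotterdam Study, second and third cohorts: "Multiple follow-up examinations of these two cohorts were conducted between 2000 and 2012". SHIP, first cohort: "Multiple follow-up examinations of this first cohort were conducted between 1997 and 2015".
- **Matching** (Missing data and matching). All matching variables are baseline values. Year of donation or inclusion enters the propensity score, but is not among the exact-matched or radius-matched variables. Follow-up time is not listed.
- **Analysis** (Statistical analysis). "For the medical outcomes a conditional linear or Cox regression analysis will be chosen as appropriate for the outcome". Linear mixed models are named for the psychological outcomes. For repeated kidney function, mixed models are named only under the donor subgroup analysis.
- **Claim** (Discussion). Average follow-up is to be ten years, and "We aim to assess the long-term consequences of live kidney donation after a decade post-donation".

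**The concern.** Two people matched on baseline age have the same age at outcome only if they are observed for the same length of time. Here the donor side reaches back to 1981 and the non-donor side to 1997 at the earliest. A donor seen at 25 years can only be set against someone seen at 18 years or less, and kidney function falls with age whether or not a kidney was given.

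A second issue remains even at equal times. A difference in level combines the one-off loss at nephrectomy with any difference in the later rate of change. The step is a true consequence of donation and belongs in the result. Whether function then declines faster than in comparable people is a separate part of the long-term question, and a single contrast cannot answer it.

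What is at stake is the interpretation of the primary comparison in a study whose stated purpose is to improve on the comparability of earlier donor studies.

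**Working it through.** **1. Follow-up spans.** Visit dates are not given. The only dating is the ethics number: "Approval of the Medical Ethical Committee was obtained (MEC-2012-519". I take visits in 2012 to 2015.

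- Donors, 2012 visits: 2012 − 2010 = 2 to 2012 − 1981 = 31 years.
- Donors, 2015 visits: 2015 − 2010 = 5 to 2015 − 1981 = 34 years.
- Rotterdam Study maximum: 2012 − 2000 = 12 years. SHIP maximum: 2015 − 1997 = 18 years. I read each window as including the baseline examination.

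**2. What year of donation or inclusion can do.** No non-donor enters before 1997, so donation years 1981–1996, 16 of 30, have no counterpart. Where counterparts exist, the variable draws start dates together through the score but does not align end dates.

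**3. How many donors lie outside the non-donor windows.** The article gives no distribution. A mean of 10 years with minimum m allows at most (10 − m)/(c − m) of donors beyond c years.

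| Visits | m | Upper bound beyond 12 y | Upper bound beyond 18 y |
|---|---|---|---|
| 2012 | 2 | 8/10 = 80% | 8/16 = 50% |
| 2015 | 5 | 5/7 = 71% | 5/13 = 38% |

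These are bounds, not estimates. For a plausible figure, assume exponential programme growth at rate r, reaching R donors a year in 2010, with R/r × (1 − e^(−30r)) = 1092. R = 90 to 140 gives r = 0.073 to 0.125. With visits at the start of 2013, 2 years after the donation window closes, the share beyond c years is (e^(−r(c−2)) − e^(−30r))/(1 − e^(−30r)):

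| R | Mean follow-up | Beyond 12 y | Beyond 18 y | Under 10 y |
|---|---|---|---|---|
| 90 | 11.9 y | 42% | 22% | 50% |
| 140 | 9.3 y | 27% | 11% | 65% |

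The means bracket the stated ten years. With 2015 visits, 35–50% are beyond 12 years and 15–28% beyond 18, but the means rise by 2 to 11.3–13.9, a poorer fit to ten.

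**4. Size of the ageing component.** Assume a decline of 0.5 to 1.0 ml/min/1.73m² per year. As an illustration, the CKD-EPI age term at fixed creatinine (a man with creatinine 85 µmol/l) takes eGFR from 91.6 at age 50 to 85.4 at 60: 6.2/10 = 0.62 per year, inside that range.

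- Early donor at 31 years: the gap is 31 − 18 = 13 to 31 − 12 = 19 years, so 13 × 0.5 = 6.5 to 19 × 1.0 = 19 against the donor.
- Average donor at 10 years, by assumed non-donor mean follow-up (plus = against donors):
  - 6 years: 4 × 0.5 to 4 × 1.0 = +2 to +4.
  - 9 years: +0.5 to +1.
  - 12 years: −1 to −2.

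**5. What one contrast contains.** Let both start at level B, with step loss D in the donor, yearly declines s₁ (donor) and s₀ (non-donor), and follow-up t (donor) and t′ (non-donor). Then

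donor − non-donor = (B − D − s₁t) − (B − s₀t′) = −D − (s₁ − s₀)t − s₀(t − t′).

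The terms are step, slope difference and unequal time. Aligning follow-up removes only the third. For illustration, assume a baseline of 90 and a step of 25–35%: D = 22.5 to 31.5, a spread of 9. A slope difference of 0.5 per year over 10 years amounts to 5 and is hidden within that spread.

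**The case against.** The article is condensed. It does not say which follow-up value is compared, and it does not rule out adjustment for time or attained age; a fuller plan may settle both. That stands, so the point concerns what the stated method can do, not what will certainly be done. It does not dispose of the point. The article assigns a longitudinal model to kidney function within donors and a different model to the between-group comparison, and no covariate can supply non-donor data beyond 18 years.

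Four stronger readings are tempting, and the document does not support them:

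- **The primary estimate is biased against donors.** The stated ten-year average lies inside both non-donor windows, and recent donors may be set against people observed for longer. At R = 120 about 32% of donors exceed 12 years, by 6.7 years on average. Spread over all donors this is 0.32 × 6.7 = 2.1 years, or 2.1 × 0.62 = 1.3 ml/min/1.73m², before any offset from recent donors. The age term also leaves serum creatinine, named alongside eGFR, unchanged.
- **Matching ignores calendar time altogether.** Year of donation or inclusion is in the propensity score. On the growth assumption, (1 − e^(−14r))/(1 − e^(−30r)) = 72–85% of donors gave in 1997 or later, so it has counterparts for most of the cohort. It remains a weak safeguard.
- **The immediate loss of a kidney is an artefact.** It is a real effect of donation, and a level difference is a legitimate total effect. The limitation is only that step and later change are not told apart.
- **All serial donor values are already in hand.** Annual checks may be done elsewhere, and the article does not say that those results are in the study database.

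**Conclusion.** The point holds in a limited form and should be fixed; it does not invalidate the study. Nothing stated aligns follow-up time or age at outcome within matched sets, and the between-group conditional linear regression cannot separate step loss from later decline.

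The distortion is potentially large for early donors (6.5 to 19 ml/min/1.73m² at 31 years). On average it is modest and of uncertain sign (about +4 to −2). Both ranges rest on the assumed yearly decline, the assumed visit dates and, for the average, the assumed non-donor mean follow-up.

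The lack of a comparator beyond 12 or 18 years needs only the calendar dates in the article and visits no earlier than 2012. With 2012 visits, it affects donations before 2000 (Rotterdam Study sets) and before 1994 (SHIP sets). Comparative statements about a decade are likewise unsupported for sets in which either side has under 10 years. That may be half or more of the donors (50–65% under the growth assumption with 2013 visits).

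**What to change.** - **Model.** Make the between-group kidney-function analysis a linear mixed model of repeated eGFR and creatinine on time since baseline, with donor time starting after the early post-donation period.
- **Estimates.** Report two quantities separately: the donor-minus-non-donor level at a stated common time, and the difference in annual slope.
- **Horizon.** Limit the comparison to time that both sides share, at most 12 years for Rotterdam Study sets and 18 for SHIP sets. Describe later donor follow-up without a comparator.
- **Single-value alternative.** If one value per person is kept, take the available donor value nearest in time since baseline to the non-donor's examination.
- **Claims.** Confine comparative statements about the period after a decade to sets in which both sides have at least 10 years.

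The cost is mainly wording and programming. Donor time beyond the non-donor windows becomes descriptive. Some annual values held by other hospitals or general practitioners would have to be retrieved or left out; if left out, say how many and for whom.

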### Outcome measures

The primary outcome is kidney function in serum creatinine and eGFR (calculated with the CKD-EPI formula) [38]. Secondary outcomes are: diastolic and systolic blood pressure as measured by data scope, incidence of hypertension and incidence of diabetes, incidence of fatal and non-fatal cardiovascular diseases, volume of the remaining kidney in cm^3^ by ultrasound (measured by experienced ultrasonographers), quality of life (measured by EuroQoL and SF-12, that can be extracted from any SF-36 [39, 40]), survival, and psychological well-being (for donors aged 45 years and higher with Hospital Anxiety and Depression Scale (HADS) [41], Center for Epidemiologic Studies Depression Scale (CESD) [42], Pittsburgh Sleep Quality Index (PSQI) [43], and questionnaires on Happiness and Life Satisfaction, and for donors aged 44 years and lower with the Beck Depression Inventory (BDI)) [44]. These outcomes will be compared between groups, but also within the donor cohort.

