### Missing data and matching

Participants from the Rotterdam Study and SHIP will be restricted from analysis if they would not qualify for live kidney donation based on the following criteria: prevalent diabetes, an eGFR < 60 ml/min/1.73m^2^, and a BMI > 40 (kg/m^2^). To account for the fact that data for covariates at baseline are not complete for all subjects, a multiple imputation approach will be utilized based on the method of chained equations [45]. Using this procedure 10 complete data sets will be created, and for each of the data sets the following steps will be performed: First, donors and non-donors will be 1:4 matched using propensity score matching based on the baseline covariates: age, gender, year of donation/inclusion, BMI, ethnicity, kidney function, blood pressure, pre-existing co-morbidity, glucose level, smoking, alcohol use and highest education degree. Exact matching will be required for gender, ethnicity, existing co-morbidity, and smoking. Progressive radius matching will be performed for age, BMI, kidney function and blood pressure. Each non-donor subject will be allowed to serve as a potential match to more than one donor. If the available data in the control group is insufficient, the target ratio of 1:4 donor:non-donor will be reduced accordingly.

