## Discussion

Recently, studies have emerged that demonstrated unfavourable outcomes after live kidney donation with regard to the long-term risk of ESRD and increased risk of mortality [13, 14]. Donors are a screened and selected population of healthy individuals and therefore it is of utmost importance to maximize both short-term and long-term donor safety. However, high quality studies on long-term outcome after live kidney donation are not very common. Till date there are nine studies in which long-term outcomes are compared between donors and selected non-donors with a follow-up of ten or more years. These studies demonstrate contradictory results regarding the incidence of morbidity and mortality following donation [15–22, 46].

There are differences in the methodology of these studies questioning the comparability of donors and the selected non-donors. No other study has looked into the long-term consequences of live kidney donation in the Dutch health care system. The nine studies were published between 1992 and 2015, with the number of donors ranging from 30 to 2269 and the average follow-up period ranging from 10.9 to 23.7 years. Also, most studies report on a selection of their entire donor cohort. We intend to include our consecutive cohort from the conception of our live kidney donor program with an average follow-up of ten years. Furthermore, due to the follow-up study visits next to registry data, we will have the current physical examination, laboratory results, and medical status. This will provide additional information on potential donors at risk for unfavourable outcomes. The previous studies derived their non-donors from siblings of the donors [17], background/general population [16, 21, 22], and population-based cohort studies [15, 18, 19, 46]. Furthermore, the matching of donors to non-donors was performed based on different characteristics, e.g. age, gender, BMI. Due to our extensive data collection of donors and the prospective data collection of our comparison group we can strive for more comparability between donors and non-donors. We intend to match our donors on all characteristics provided in previous studies and more for a better comparability of donors and non-donors.

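### The published plan states no step that aligns time since baseline when eGFR, creatinine and blood pressure are compared between donors and matched non-donors, so differences in attained age can enter the primary contrast

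*Protocol article*

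**What the plan says.** All references are to the protocol article.

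- **Outcome measures**: "The primary outcome is kidney function in serum creatinine and eGFR". No time after baseline is attached to it. Blood pressure is a secondary continuous outcome.
- **Missing data and matching**: "First, donors and non-donors will be 1:4 matched using propensity score matching based on the baseline covariates". The list is "age, gender, year of donation/inclusion, BMI, ethnicity, kidney function, blood pressure, pre-existing co-morbidity, glucose level, smoking, alcohol use and highest education degree". Exact matching is then required for gender, ethnicity, co-morbidity and smoking, and radius matching for age, BMI, kidney function and blood pressure. Year is in neither of these two lists. Length of follow-up is in none of the three.
- **Statistical analysis**: between groups, "For the medical outcomes a conditional linear or Cox regression analysis will be chosen as appropriate for the outcome". For kidney function as a repeated measure, "mixed models will be chosen for repeated variables, e.g. kidney function and quality of life", but that sentence concerns the donor subgroup analysis only.
- **Participants and procedure (donors)**: donation took place from 1981 through 2010. Surviving donors are invited to a study visit that comes on top of annual monitoring of kidney function and blood pressure.
- **Participants and procedure (non-donors)**: SHIP examinations run from 1997 to 2015. For the two Rotterdam cohorts, "Multiple follow-up examinations of these two cohorts were conducted between 2000 and 2012". On recruitment to the Rotterdam Study as a whole, "As of 2008, 14,926 subjects aged 45 years or over were included".
- **Discussion**: the donor cohort is described "with an average follow-up of ten years".

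**The concern.** Within a set matched on baseline age, attained age at measurement is baseline age plus elapsed time. If the donor and the controls are measured at different times since baseline, they are compared at different ages. Conditioning on the matched set does not remove that difference, because it arises after matching. Cox models allow for unequal follow-up through censoring. A linear model of eGFR, creatinine or blood pressure does not, unless time is in it or the measurements are aligned beforehand.

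At stake is the primary contrast. If kidney function declines with age, a set whose donor is measured later than its controls shows a deficit that is partly ageing, and a set whose donor is measured earlier shows apparent protection. The mix would vary with the era of donation, in a study whose stated advantage is better comparability of donors and non-donors.

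**Working it through.** The article gives no sample size calculation, effect size or SD, so there is no design figure to reproduce. The check has two parts: what the calendar dates imply, and what a gap in elapsed time could do.

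**1. Elapsed time available in each group**

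- SHIP controls: at most 2015 − 1997 = 18 years.
- Rotterdam controls: at most 2012 − 2000 = 12 years. A participant who entered in 2008 would have at most 2012 − 2008 = 4.
- Donors at the study visit: the year of the visit is not given. The ethics reference carries the year 2012, so 2012 is taken as the earliest plausible year and 2015 as an alternative. Elapsed time is 2 to 31 years for a 2012 visit (2012 − 2010, 2012 − 1981) and 5 to 34 years for a 2015 visit.

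Years by which a donor's elapsed time at the visit exceeds the longest possible control follow-up:

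| Donation year | Elapsed, 2012 visit | Over SHIP (18) | Over Rotterdam (12) | Elapsed, 2015 visit | Over SHIP | Over Rotterdam |
|---|---|---|---|---|---|---|
| 1981 | 31 | 13 | 19 | 34 | 16 | 22 |
| 1990 | 22 | 4 | 10 | 25 | 7 | 13 |
| 1995 | 17 | 0 | 5 | 20 | 2 | 8 |
| 2000 | 12 | 0 | 0 | 15 | 0 | 3 |
| 2005 | 7 | 0 | 0 | 10 | 0 | 0 |
| 2010 | 2 | 0 | 0 | 5 | 0 | 0 |

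For the earliest donors, no control examination can match the study visit in elapsed time. For recent donors alignment is possible, but nothing stated selects the examination that would achieve it. A 2010 donor seen at 2 years could be set against a much later SHIP examination.

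**2. What year of donation or inclusion can do**

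Of the 30 donation years, 1997 − 1981 = 16 precede any SHIP examination and 2000 − 1981 = 19 precede any Rotterdam examination used. For those years there is no control baseline of the same year. For later years, year is one component of a score and so aligns the start of follow-up loosely. It does not fix which examination supplies the outcome. These are counts of years, not of donors; the distribution of donors over years is not given.

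**3. Illustration of size**

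From the article: 1092 donors and a target response of 70%, giving 0.70 × 1092 ≈ 764 donors, and at 1:4, 4 × 764 = 3056 control slots. Assumed, not in the article: eGFR decline of 0.5–1.0 ml/min/1.73m2 per year, SD 15 (range 12–20), and a two-sided 5% test.

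- SE = SD × √(1/764 + 1/3056) = 15 × 0.04045 = 0.61. This ignores correlation within sets and reuse of controls.
- False difference = mean gap in elapsed time × annual decline.
- False-positive rate with no donation effect = P(|Z + difference/SE| > 1.96).

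| Mean net gap (assumed) | False difference | In SE (SD 15) | False-positive rate, SD 15 |
|---|---|---|---|
| 1 year | 0.5–1.0 | 0.8–1.6 | 13–38% |
| 2 years | 1.0–2.0 | 1.6–3.3 | 38–91% |
| 5 years | 2.5–5.0 | 4.1–8.2 | 98% or more |

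Over SD 12–20, the 2-year row spans 24–98%. The gap here is the net average over all sets. Gaps of opposite sign partly cancel, and the article does not let the net be calculated.

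**The case against.** The strongest reply is that a condensed article lists no covariates for any model. Elapsed time is unlisted rather than excluded, and a full analysis plan may contain it. That stands: a reader might infer that ageing will be counted as an effect of donation, but the text supports only that it can be, if the stated matching and model are applied as written. The reply does not dispose of the point, because a time term alone cannot help beyond 18 years, where no control data exist and adjustment would be extrapolation.

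Other stronger readings are also unsupported:

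- **That the donor outcome comes from one visit.** Donors are monitored annually and the visit supplements this, so earlier donor values may be available for alignment.
- **That a 10-year donor will typically meet a 4-year control.** A 4-year ceiling belongs to a control included around 2008. A donor at 10 years at a visit in 2012–2015 gave in 2002–2005, so the pair differs by 3 to 6 years on year of donation or inclusion, which the propensity score works against. A gap of 6 years is not shown to be usual.
- **That the bias must run against donors.** Mean donor follow-up of ten years lies inside both control windows, and recent donors may be measured earlier than their controls.
- **That the psychological mixed models share the problem.** Their fixed effects are not listed, and nothing in the article shows it.

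**Conclusion.** The point holds as a weakness in the stated primary comparison. The matching covariates are all baseline variables, the between-group model for continuous medical outcomes carries no stated time element, and the model suited to repeated kidney function is named only within donors. The article's own dates make unequal elapsed time unavoidable at the study visit for the earliest donors, and leave it uncontrolled for the others.

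Net direction and size are not derivable from the article. The illustration (1.0–2.0 ml/min/1.73m2 for a 2-year mean gap) rests on an assumed rate of decline, SD and gap; it shows only that a modest net gap could matter at this sample size. The 2–31 year range rests on a visit in about 2012, which is inferred. Time-to-event outcomes analysed by Cox regression are outside the point.

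**What to change.** 1. In the matching rule, state that for each set the donor and control measurements used are those closest in time since baseline, drawing on annual donor monitoring values where available.
2. Include time since baseline in the between-group linear model, or use a mixed model with time and group-by-time terms.
3. Limit the primary contrast to elapsed times observed in both groups: at most 18 years against SHIP and 12 against the Rotterdam cohorts.
4. Report the distribution of the within-set gap in elapsed time.

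With measurements compared at equal elapsed time, this source of bias is removed and, in the illustration, the false-positive rate returns to 5%.

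The text change is short, but there are costs. Dated annual values must be assembled, and some of that monitoring takes place at other hospitals or with general practitioners. Donor measurements beyond the control windows leave the primary contrast and are reported within donors only. This narrows the between-group evidence at the longest follow-up, where no control data exist to support it.
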